#### Data Collection

##### RCT

The primary outcome measures will be the proportion of patients who achieve target doses and the time to dose optimization. Additional measures will include patient health outcomes (including, but not limited to, New York Heart Association [NYHA] class, LVEF, and brain natriuretic peptide [BNP] levels), the number of visits and/or calls required to achieve target doses, and health care resource utilization.

Information will be obtained by reviewing the patients’ electronic patient record (EPR) charts and Medly data and documentation throughout the study by the study coordinator. Baseline and poststudy medications and dosages for each patient and baseline and poststudy clinical measures, including NYHA class, LVEF, and BNP levels, will be determined through manual EPR chart reviews. Health care utilization will primarily be determined through EPR chart reviews. However, this information will be supplemented through patient self-reporting to account for situations in which patients use services outside of UHN. Data regarding the titration process, such as the number of visits and/or phone calls performed, actions undertaken, and any adverse events that occurred throughout the study, will be documented by the study coordinator. The number of visits, phone calls, and total contact points will be recorded in detail for each group to determine the impact of remote titration on the GDMT optimization process.

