**Objective:**

The primary objective of this study is to evaluate the impact of remote titration facilitated by telemonitoring on health care outcomes, with a primary outcome measure being the proportion of patients achieving target doses. The secondary objective is to identify the barriers and facilitators that can affect the implementation and effectiveness of the intervention.

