### Objectives

This study aims to explore how the combination of remote titration and telemonitoring affects GDMT optimization compared with standard of care. The study takes a dual focus in assessing both the clinical effectiveness and implementation of the intervention. The primary objective of this study is to evaluate the impact of remote titration facilitated by telemonitoring on health care outcomes, including the proportion of patients achieving target doses, time to dose optimization, and patient health outcomes. The secondary objective of this study is to obtain a deeper understanding of the experiences of clinicians and patients with HF participating in the remote titration program to identify factors that affect the implementation of the intervention.

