### Sample Size Calculation

One of the main outcome measures of this study, the number of visits required to complete titration, was used to calculate the initial sample size based on data obtained from the existing literature. Assuming biweekly titration over a period of 3 to 6 months (ie, 9±3 visits in total for the control group) as recommended by HF guidelines [10,19], a reduction of at least 35% in the number of visits for the intervention group, 80% power, and α=.05 (two-sided), the sample size per group was calculated to be 16. Furthermore, assuming that as much as 30% of the patients may be lost to follow-up or cannot be titrated, the sample size per group became 21. Hence, 42 patients were enrolled for the internal pilot portion of the study.

Data from the internal pilot and the literature were combined to perform the final sample size calculation. It was determined that the initially selected primary outcome measure of the number of visits required to achieve titration was not appropriate because clinic visits were strongly affected by external factors unrelated to the intervention. Many patients in the control group attended very sporadic clinic visits, which resulted in a slow and unpredictable titration process. Therefore, the new calculation was based on an alternative primary outcome measure, which was the proportion of patients achieving target doses. In the pilot cohort, 18 of 21 patients (86%) in the intervention group and 10 of 21 patients (48%) in the control group completed titration within 6 months of enrollment. According to an expert panel conducted by the Canadian Cardiovascular Society, most physicians (55%) believed that the entire triple therapy titration to maximum tolerated or target doses should be completed within 4 months, 93% believed that this should be done within 6 months, and all respondents agreed that every titration would not necessarily require a face-to-face visit [19]. The titration completion rates reported in the literature vary, and the timelines are not always clear. However, multiple studies reported that 17% to 43% of patients achieve target doses within 3 to 6 months [12,20,21].

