In light of the varying ranges provided by available data and to ensure that the sample size of the full study would be sufficient to detect statistical significance, a higher completion rate among those available was used for the control group, and a slightly more conservative completion rate was used for the intervention group. Therefore, rates of 45% and 75% were used for the control and intervention groups, respectively. The calculation assumed a power of 80%. An alpha of .025 (two-sided) was used, instead of .05, to account for the single interim analysis conducted. On the basis of this, the sample size per group was calculated to be 49. Furthermore, assuming that up to 10% of the patients may be lost to follow-up or cannot be titrated (based on the observed attrition rate in the internal pilot), the sample size per group was calculated to be 54. Hence, the overall sample size of the study is 108 patients.

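### The sample size rests on one primary outcome but Data Collection names two, and the .025 alpha is used wholly on the first

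*Protocol article*

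**What the plan says.** The protocol article describes the primary outcome in four places, and they do not match.

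- **Abstract, Objective:** "with a primary outcome measure being the proportion of patients achieving target doses". One outcome is named.
- **Objectives:** the primary objective covers "the proportion of patients achieving target doses, time to dose optimization, and patient health outcomes". Time stands beside the proportion.
- **Sample Size Calculation:** after the internal pilot, the number of visits was dropped as primary outcome and "the new calculation was based on an alternative primary outcome measure, which was the proportion of patients achieving target doses". One outcome, in the singular.
- **Data Collection, RCT:** "The primary outcome measures will be the proportion of patients who achieve target doses and the time to dose optimization". Two outcomes. Health outcomes, visits, calls and resource use follow as additional measures.

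On the error level, Sample Size Calculation says: "An alpha of .025 (two-sided) was used, instead of .05, to account for the single interim analysis conducted". The planning figures concern the proportion only: "rates of 45% and 75% were used for the control and intervention groups, respectively", with 80% power, giving 49 per group, 54 after a 10% attrition allowance, and 108 in all. Data Analysis, RCT, lists chi-square tests for binary data and t or Mann-Whitney tests for other between-group data.

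**The concern.** Which outcomes are primary, and how many, is a core protocol item, and here it is stated in two ways. The reduced alpha is justified by the interim look alone, and the sample size uses all of it for the proportion. A second primary outcome therefore has no share of the error and no stated place in an order.

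Two things are at stake. First, if success on either outcome were taken as a positive trial, the type I error would exceed the planned level. Second, a split result would have no agreed reading. Such a split is realistic: the Discussion describes a carvedilol titration trial with no statistical difference in the proportion reaching target doses but a significantly shorter time to the final dose with remote titration (mean 33.6 v 63.7). The same pattern here could be reported as a success or a failure, depending on which section is followed.

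**Working it through.** **1. Reproduce the plan's figure.** Inputs from Sample Size Calculation: 45% v 75%, two-sided alpha .025 (z = 2.241), power 80% (z = 0.842), 1:1 allocation.

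- Arcsine formula: h = 2·asin(√0.75) − 2·asin(√0.45) = 0.624; n = 2(2.241 + 0.842)²/h² = 48.9, so 49 per group.
- Normal approximation with pooled variance under the null: 49.4, so 50.
- Attrition: 49 × 1.10 = 53.9, so 54; total 108.

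The stated 49 is reproduced with the whole .025 on the proportion. Nothing is left over for a second outcome.

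**2. Error at one analysis if either outcome suffices, each at .025.**

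- Upper bound: .025 + .025 = .050.
- Independent tests: 1 − 0.975² = .0494.
- Correlated tests (bivariate normal):

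| Correlation | Error |
|---|---|
| 0.5 | .046 |
| 0.7 | .043 |
| 0.9 | .036 |
| 0.96 | .032 |

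The correlation depends on how time is analysed, which the article does not fix. Null trials were simulated with 49 per group, exponential times, a 6-month cut-off and 45% to 60% completing (all assumptions):

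- chi-square plus log-rank: .029 to .033;
- chi-square plus Mann-Whitney on all patients, non-completers tied at 6 months: .031 to .040;
- chi-square plus Mann-Whitney among completers only: .044 to .052, which is the near-independent case within simulation error.

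**3. Error over two looks.** The .025 is a per-analysis level chosen to protect an overall .05, so the total is the better benchmark. Assume an information fraction of 42/108 = 0.39 (pilot size over final size), .025 at each look, and both outcomes tested at each look.

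| Outcomes that can win | Correlation | Total error |
|---|---|---|
| Proportion only | – | about .045 |
| Either of two | 0.96 | .057 |
| Either of two | 0.9 | .063–.064 |
| Either of two | 0.7 | .076 |
| Either of two | 0 | .087 |

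With one outcome the plan stays under .05. With two and an either-wins rule it exceeds .05 at every correlation checked.

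**4. Rules that cause no inflation.** If both outcomes must be significant, or time is tested only after a significant proportion, the error per analysis stays at or below .025.

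**5. Price of an alpha split.** With .0125 on the proportion (z = 2.498), the pooled formula gives 59 per group (arcsine 58). With attrition that is 65 (59 × 1.1) or 66 (59/0.9), so 130 to 132 in total. Keeping 49 evaluable per group at .0125 gives 71.2% power; 54 evaluable gives 76.4%.

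**The case against.** A reader might infer that the family-wise error simply doubles. The document does not support that. Doubling is the ceiling, approached only when the two tests are almost independent. Time to optimization and the proportion optimized share the same events, so a time-to-event test would be strongly correlated with the chi-square test. The near-independent case needs a comparison of times among completers only. The list of t and Mann-Whitney tests makes that possible, but nothing restricts those tests to completers.

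A reader might also infer that either outcome alone makes the trial positive. The article never says so, and silence is not a rule. Nor is there support for a scenario with both outcomes tested at .05, since the stated level is .025.

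Two further points stand. The abstract's wording, with its indefinite article, is not strictly exclusive, and Objectives and Data Collection agree in giving time a place; the clear conflict is between Sample Size Calculation and Data Collection. Basing the sample size on one of two primary outcomes is also not in itself an error. Finally, alpha allocation and test order are commonly left to an analysis plan that is not shown, so their absence from a condensed article is not the fault here.

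What remains is that the article states the number of primary outcomes in two ways. An analysis plan cannot settle that without departing from one of the two sections.

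**Conclusion.** The concern holds in a limited form. The sections disagree on whether there is one primary outcome or two, and the whole .025 goes to the proportion.

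The effect on error is conditional. If either outcome suffices, error per analysis rises from .025 to somewhere between about .029 and .049, with .05 as the bound. Over two looks the total is about .057 to .087 against the intended .05. These figures rest on the assumed correlations, the simulation model, the information fraction of 42/108 and testing of both outcomes at both looks. Under a both-must-win or fixed-order rule the inflation is nil.

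The contradiction is certain and the inflation is only possible. It should be corrected before the final analysis; it does not invalidate the sample size for the proportion.

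**What to change.** Make the abstract, Objectives, Sample Size Calculation and Data Collection agree. The simplest course is to name the proportion, on which the sample size rests, as the only primary outcome at two-sided .025. Time to dose optimization becomes a key secondary outcome, tested at the same level only if the primary is significant. The 49 (54) per group stand unchanged.

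The cost is that time can no longer rescue a null primary result. The change also needs a documented and justified amendment before the final analysis, because pilot results by arm (18 of 21 v 10 of 21) have been seen and 76 of 108 patients had been recruited at the reported date.

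If both outcomes are to stay primary, state whether both must be significant. If so, alpha is unchanged, but the power to win on both needs its own calculation. If either suffices, state the alpha split and restate the power: at .0125 the proportion has about 71% with 49 evaluable per group, and restoring 80% takes about 130 to 132 patients in total.

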**Health service utilization**					
	Number of HF^b^-related hospitalizations since enrollment	N/A	✓	✓	✓
	Number of days in the hospital since enrollment	N/A	✓	✓	✓
	Number of emergency department visits since enrollment	N/A	✓	✓	✓
	Number of clinic visits or phone calls since enrollment	N/A	✓	✓	✓

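### The count of contacts needed to reach target doses has a value only in patients who succeed, so comparing it between arms is not protected by randomization

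*Protocol article*

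**What the plan says.** The Data Collection (RCT) section of the protocol article states: "The primary outcome measures will be the proportion of patients who achieve target doses and the time to dose optimization". Among the additional measures it then names "the number of visits and/or calls required to achieve target doses". The Data Analysis (RCT) section assigns between-arm comparisons of poststudy data to a t test or a Mann-Whitney test, according to distribution.

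The Sample Size Calculation section explains that a visit count was the initial primary outcome. It was dropped because "clinic visits were strongly affected by external factors unrelated to the intervention". For the replacement outcome, "rates of 45% and 75% were used for the control and intervention groups, respectively". The internal pilot found that "18 of 21 patients (86%) in the intervention group and 10 of 21 patients (48%) in the control group completed titration within 6 months".

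Contacts are also recorded in a form not worded as limited to achievers. Data Collection has visits, calls and total contacts documented for each group, and Table 1 lists "Number of clinic visits or phone calls since enrollment" at the interim analysis, at titration completion and at the 3-month follow-up.

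**The concern.** The named measure is defined by reaching target. It exists in a subgroup that is formed after randomization and identified by a primary outcome. The better the intervention works, the more the achievers in the two arms differ in kind. If remote titration brings slower patients to target who would not have got there under office titration, those patients add high counts to the intervention arm, while their control counterparts add nothing. A difference can then appear when the contacts needed per patient are the same in both arms, or a real saving can be hidden.

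At stake is what the trial can say about the effort needed to optimize therapy, which is the stated reason for recording contacts. The reason given for dropping the visit count as primary, outside influences on attendance, is a different problem and does not deal with this one.

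**Working it through.** **The plan's own figures.** For 45% vs 75% the assumptions are "The calculation assumed a power of 80"% and "An alpha of .025 (two-sided) was used, instead of .05". The mean rate is 0.60, and the pooled formula gives

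n = [2.241·√(2·0.60·0.40) + 0.842·√(0.45·0.55 + 0.75·0.25)]² / 0.30² = (1.553 + 0.555)² / 0.09 ≈ 49.4,

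which is 50 rounded up, against the stated 49. The stated figure reproduces within rounding, and 49 evaluable patients per arm is used below.

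**Who has a value.** At the planned rates, 49·0.45 ≈ 22 control and 49·0.75 ≈ 37 intervention patients would have a count, so 55% and 25% would not. In the pilot, 11/21 (52%) and 3/21 (14%) had not completed titration by six months.

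**Bias with no true arm difference.** Inputs: visits needed have mean 9 and SD 3 (the control-group design assumption in Sample Size Calculation), taken here as the same in both arms. A patient succeeds when a latent standard normal variable falls below z_p, where p is the arm's success rate. ρ is the correlation of that variable with visits needed. The document gives no ρ, so it is an assumption and is varied from 0 to 1. Then

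mean among achievers = 9 − 3·ρ·φ(z_p)/p.

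The ratio φ(z_p)/p is 0.880 at p = 0.45, 0.424 at 0.75, 0.836 at 10/21 and 0.263 at 18/21. For example, with ρ = 0.5 at the planned rates, control = 9 − 1.5·0.880 = 7.68 and intervention = 9 − 1.5·0.424 = 8.36, a gap of 0.68.

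Rejection is for Student's t test among achievers at two-sided .05, simulated with 49 per arm.

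| Rates | ρ | Control mean | Intervention mean | False gap (visits) | Rejection |
|---|---|---|---|---|---|
| Planned 45%/75% | 0 | 9.00 | 9.00 | 0 | about 5% |
| | 0.3 | 8.21 | 8.62 | 0.41 | about 7–8% |
| | 0.5 | 7.68 | 8.36 | 0.68 | about 14% |
| | 1 | 6.36 | 7.73 | 1.37 | about 70% |
| Pilot 10/21, 18/21 | 0 | 9.00 | 9.00 | 0 | about 5% |
| | 0.3 | 8.25 | 8.76 | 0.52 | about 10% |
| | 0.5 | 7.75 | 8.61 | 0.86 | about 20% |
| | 1 | 6.49 | 8.21 | 1.72 | about 86% |

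The Mann-Whitney test behaves similarly (about 88% in the last row). Wherever ρ > 0 the intervention achievers show the higher count, so in this model the bias works against the intervention.

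**The case against.** The strongest reply is that the article nowhere restricts the analysis to achievers. The test sentence is generic, and the handling of patients without a value is commonly left to a statistical analysis plan, which is not shown. It is right that no achievers-only rule is stated and that a missing rule would be no finding. But the difficulty is in the definition: contacts required to reach target cannot be stated for someone who did not reach it, and any value given to such a patient changes the measure.

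Three further points stand and limit the finding.

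- Contacts since enrollment are already recorded for both groups. The named outcome stays as it is, but the repair is cheap. Table 1 alone does not supply it, since two of its three time points follow titration completion and the third is the interim analysis.
- A reader might infer from the pilot that the count is missing for 52% of controls. The document does not support that. The 10/21 and 18/21 are completions within six months, the measure has no six-month limit, and titration also ends at a maximum tolerated dose. Some of the remaining patients may have a count later.
- A reader might also take the 1.7-visit gap and the 86% rejection as the expected size. They are the extreme case, in which visits needed fully determine success. The Sample Size Calculation section attributes slow control titration to sporadic attendance, which points to a weaker link.

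**Conclusion.** The concern holds for one additional measure. As defined, it has a value only in patients who reach a primary outcome that is expected to differ by 30 percentage points between arms, so a between-arm test of it lacks the protection of randomization. The bias is zero only if the contacts a patient needs are unrelated to success. For correlations of 0.3 to 0.5 the false gap is about 0.4 to 0.9 visits, with rejection of about 7% to 20% at a nominal 5%. The extreme is 1.4 visits (planned rates) or 1.7 visits (pilot rates).

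These figures rest on the 9±3 assumption in both arms, normality, 49 evaluable per arm and an assumed correlation. Neither size nor direction can be fixed from the document. It would be wrong to conclude that the trial's main result is compromised: the proportion reaching target, the time to dose optimization and the sample size do not depend on this measure.

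**What to change.** Make the between-arm comparison the number of clinic visits, calls and total contacts from enrollment to one common cut-off, for example six months, in all randomized patients whether or not target was reached. Use a test suited to counts: the Mann-Whitney test already planned, or a count model. Keep contacts to target among achievers as a description by arm, without a test.

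The cost is a change of wording and one fixed cut-off. The coordinator already documents visits and calls throughout the study, so no new data source is needed.

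There is a small downside. The all-patient total measures contact use, not contacts needed per success, and a low control count may reflect sporadic attendance and not efficiency. It should be reported beside the proportion reaching target in each arm.

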##### Qualitative Study

The qualitative study will aim to identify the barriers to and facilitators for implementation. Semistructured one-on-one interviews will be conducted with participants to explore their views on various aspects of the remote titration program. Patients randomized into the intervention group will be interviewed in a quiet and private space within the clinic or over the telephone. Interviews are expected to last between 15 and 30 min. Additional interviews will be conducted until data saturation is reached and the interviewer determines that no new pertinent information is being collected. Health care providers from the Heart Function Clinic who participate in the remote titration program will also be interviewed. The individual interviews are expected to last between 20 and 45 min and will be conducted in the clinician’s office or over the telephone. All interviews will be audio-recorded and transcribed for subsequent analysis.

The schedule for data acquisition is shown in Table 1.

**Table 1 table1:** Schedule for data acquisition indicated by checkmarks at the specified time point.

Data collected		Baseline	Interim analysis	Titration completion	3-month follow-up
Demographics		✓	N/A^a^	N/A	N/A
**Health service utilization**					
	Number of HF^b^-related hospitalizations since enrollment	N/A	✓	✓	✓
	Number of days in the hospital since enrollment	N/A	✓	✓	✓
	Number of emergency department visits since enrollment	N/A	✓	✓	✓
	Number of clinic visits or phone calls since enrollment	N/A	✓	✓	✓

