The titration process is terminated when patients reach target doses or maximum tolerated doses. A follow-up clinic appointment is scheduled within 3 months of titration completion, as per the standard of care. Throughout this process, the importance of patients’ adherence to program requirements in terms of daily measurements and symptom reporting is emphasized and strictly monitored to ensure prompt identification of potential changes in their condition.

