#### Data Analysis

##### RCT

Descriptive, parametric, and nonparametric statistics will be performed. Statistical analyses will be selected in accordance with the data under review and the required level of comparison: McNemar tests will be performed on binary baseline and poststudy data, whereas chi-square tests will be performed to compare binary poststudy data between the intervention group and the control group; paired Student *t* tests and Wilcoxon signed-rank tests will be performed on baseline and poststudy data for normally and not normally distributed data, respectively. Independent Student *t* tests and Mann-Whitney tests will be performed to compare poststudy data between the intervention group and the control group for normally and not normally distributed data, respectively.

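### Hospital use and clinical measures are timed from each patient's own titration completion, so the arms are compared over unequal exposure and at unequal times since randomization

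*Protocol article*

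**What the plan says.** The caption of Table 1 reads "Schedule for data acquisition indicated by checkmarks at the specified time point". Its columns are baseline, interim analysis, titration completion and 3-month follow-up. None of the post-baseline columns is a fixed time after randomization.

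- **Utilization.** HF hospitalizations, hospital days, emergency visits and contacts are running totals, for example "Number of days in the hospital since enrollment".
- **Clinical measures.** BNP and NYHA class are read at all four times. LVEF is read only at baseline and at the 3-month follow-up.
- **What ends titration.** Under Intervention Versus Control Groups: "The titration process is terminated when patients reach target doses or maximum tolerated doses". No calendar limit is given. The text continues: "A follow-up clinic appointment is scheduled within 3 months of titration completion, as per the standard of care".
- **Source of the data.** Under Data Collection, "baseline and poststudy clinical measures, including NYHA class, LVEF, and BNP levels, will be determined through manual EPR chart reviews".
- **Analysis.** Under Data Analysis, "chi-square tests will be performed to compare binary poststudy data between the intervention group and the control group". For other data, "tests and Mann-Whitney tests will be performed to compare poststudy data between the intervention group and the control group". No adjustment for length of follow-up is named.
- **Expected speed.** Sample Size Calculation reports that, counted from enrollment, "18 of 21 patients (86%) in the intervention group and 10 of 21 patients (48%) in the control group completed titration within 6 months", and it describes control titration as slow and unpredictable.

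**The concern.** The time anchor is an outcome. Time to dose optimization is one of the two primary measures, and the trial exists to shorten it. A total that runs from enrollment to that event stops earlier in the arm that finishes earlier. With the same monthly rate of hospital use in both arms, the intervention arm would still show fewer hospitalizations, hospital days and emergency visits.

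NYHA class, BNP and LVEF are read sooner after randomization in the faster arm, so treatment effect and elapsed time are mixed. Patients still titrating have no scheduled assessment, other than possibly the interim one, until they complete. At 6 months in the pilot that was 11 of 21 control patients (52%) and 3 of 21 intervention patients (14%).

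Data Collection also gives the primary proportion no time window, although the pilot rates behind its planning are 6-month rates. The Objectives section places patient health outcomes inside the primary objective, so these comparisons will be read as evidence of benefit.

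**Working it through.** **The plan's own figure.** With 45% versus 75%, two-sided alpha 0.025 and 80% power, the pooled formula is n = [2.241·√(2·0.60·0.40) + 0.842·√(0.45·0.55 + 0.75·0.25)]² / 0.30² = 49.4 per group. The plan states 49 (rounding up gives 50). Then 49 × 1.10 = 53.9, stated as 54, and 108 overall. This rests on the completion proportion alone, so a change in outcome timing does not affect it.

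**Inputs from the documents.** Completion by 6 months, control versus intervention: 45% versus 75% (design) and 10/21 versus 18/21 (pilot).

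**Assumptions, not in the documents.** Completion times are exponential; the follow-up falls exactly 3 months after completion (the text says within 3 months); monthly event rates are equal in the two arms; the design rates are 6-month rates.

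**Monthly hazards**, λ = −ln(1 − p)/6:
- Design: control 0.0996, intervention 0.231.
- Pilot: control 0.108, intervention 0.324.

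**Mean time to completion**, under alternative and mutually exclusive treatments of patients still titrating:
- Completers by 6 months only: 1/λ − 6(1 − p)/p. Design control: 10.04 − 6·0.55/0.45 = 2.70. Design intervention: 4.33 − 6·0.25/0.75 = 2.33.
- Everyone, titration capped at c months: (1 − e^(−λc))/λ. Design, c = 6: 0.45/0.0996 = 4.52 and 0.75/0.231 = 3.25.
- No cap: 1/λ. Design: 10.04 and 4.33.

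Adding 3 months gives mean exposure to the follow-up, in months:

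| Scenario | Design: control / intervention | Ratio | Pilot: control / intervention | Ratio |
|---|---|---|---|---|
| Completers by 6 months only | 5.70 / 5.33 | 1.07 | 5.68 / 5.08 | 1.12 |
| Capped at 6 months | 7.52 / 6.25 | 1.20 | 7.42 / 5.64 | 1.31 |
| Capped at 12 months | 10.00 / 7.06 | 1.42 | 9.73 / 6.02 | 1.62 |
| No cap | 13.04 / 7.33 | 1.78 | 12.28 / 6.08 | 2.02 |

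At the completion reading itself, without the added 3 months, the ratios are larger: 1.16, 1.39, 1.73 and 2.32 (design) and 1.29, 1.67, 2.23 and 3.01 (pilot).

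**Effect on a test.** In a simulation (49 per arm, 12-month cap plus 3 months, equal Poisson rates of 0.05 to 0.1 per month, 2,000 runs per setting), a nominal 5% Mann-Whitney test on raw counts rejected in 16% to 29% of runs at the design rates and 28% to 43% at the pilot rates. The event rates and the cap are assumptions.

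**Patients with a completion date by 6 months, of 54 per arm**, control versus intervention: 24.3 versus 40.5 (design) and 25.7 versus 46.3 (pilot).

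**The case against.** The strongest reply is that Table 1 is a collection schedule, not an analysis rule. The term poststudy is not defined, charts are reviewed throughout the study, and a full protocol or SAP could set a cut-off or a rate-based analysis. That is possible. But what the article does state is patient-specific reading times, running totals and unadjusted two-group tests, and together these produce the imbalance.

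Several stronger readings are tempting, and the documents do not support them.

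- **That 52% of control patients never complete.** The pilot figure is patients not complete by 6 months, and some complete later. The plan's own allowance for patients lost or who cannot be titrated is up to 10%.
- **That the exposure gap is always large.** If only patients complete by 6 months are counted, exposure to the follow-up differs by only about 7% to 12%. The larger ratios need later completers, or patients still titrating, to be assessed as well. One cannot claim that non-completers drop out of the comparison and also quote a ratio that includes them.
- **That contact counts are biased in the same way.** Data Collection defines that outcome as visits and calls needed to reach target doses. Counting to completion is what it means, and fewer contacts through faster completion would be a real effect.
- **That the clinical measures favor the intervention.** For NYHA class, BNP and LVEF the direction is uncertain.
- **That the primary result is undermined.** The proportion complete within 6 months is unaffected if that window is used; the article only fails to restate it with the outcome.

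**Conclusion.** The point holds for hospitalizations, hospital days and emergency visits, and for the timing of NYHA class, BNP and LVEF. Given equal event rates and faster completion with the intervention, raw counts lean toward the intervention in every scenario examined. Control exposure to the 3-month follow-up is about 7% to 102% higher. Where the truth falls in that range depends on any follow-up cap and on how patients still titrating are handled, neither of which the article states, and on the exponential assumption. Completion here includes stopping at maximum tolerated dose, not only reaching target dose.

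It would go too far to say that a null effect on hospital use must appear as a benefit, because that depends on the unstated cut-off and on event rates the article does not give. What can be said is that the schedule as written does not protect against it.

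**What to change.** 1. For between-arm comparisons of hospitalizations, hospital days and emergency visits, count events over one common window from randomization for every randomized patient, whatever the titration status. Six months is a natural example, since it is the window of the pilot rates used in planning. The alternative is a count model with log follow-up time as offset; it assumes a roughly constant event rate over follow-up, so the common window is cleaner.
2. Take NYHA class, BNP and LVEF from the chart value nearest a common date from randomization, within a stated window, again whatever the titration status.
3. State that the primary proportion is assessed at the same 6 months.
4. Keep the number of visits and calls required to achieve target doses as a completion-anchored outcome.

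The cost is a changed date rule in a chart review that is already planned. Running totals can be cut at any date. Some chart values will fall outside the window and be missing. LVEF is the most exposed, because it is scheduled only once after baseline and control echocardiograms are done as required. The sample size of 108 does not change.
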